# OUTCOME EVALUATION

## 9.1 Definitions

*Missed appointment* Participant fails to attend a routine appointment within 7 days of a scheduled appointment or have not attended ART refill visit within 7 days of scheduled appointment

*Unscheduled visit* Any clinic visit that is not a scheduled appointment

*Pubertal delay* Appropriate Tanner Stage testicular size for boys and breast development for girls not achieved for age

*Stunting* Height-for-age z-scores using WHO reference Standards

*Wasting* Weight-for-age z-scores using WHO reference Standards

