## 1.2 Aims

The objective of the study is to investigate whether a package of services at primary care level will adequately meet the needs of vertically HIV-infected children and adolescents, or alternatively whether further decentralisation to provide community-level HIV testing and/or treatment support is required.

Specific aims are:

1. To investigate the impact of treatment support provided by lay volunteers to households with one or more HIV-infected children aged 6-15 years on adherence and retention into HIV care.
2. To investigate the effectiveness of routine facility-based HIV testing and counselling in reducing rates of undiagnosed HIV infection among children aged 6-15 years in the community, over a relatively short period of time.
3. To assess the effect of ART on lung function and growth in HIV-infected children aged 6-15 years.

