## 2.2 Complications of longstanding HIV infection

Late diagnosis in children is associated not only with a risk of the well-recognised HIV-associated infections, but also with risk of chronic conditions that are not manifest in infants or adults. Nearly 50% of older HIV-infected children currently in care have life-threatening chronic lung disease, associated with severe respiratory insufficiency, hypoxia, and cor pulmonale.17-18

We have recently shown that constrictive obliterative bronchiolitis (OB) is the likely major underlying cause.17 OB affects the small airways, causing airflow limitation and hypoxic lung disease. It is difficult to diagnose (requiring high resolution CT scan, not chest radiography), and tends to be irreversible once established. OB can result from a number of insults, including post-adenovirus infection, and is an integral feature of the pathology of cystic fibrosis and rejection following lung transplantation, with some evidence for genetic predisposition to severe forms.19-21 OB has not been recognised in Western cohorts, suggesting either a geographical variability (e.g. due to more frequent exposure to respiratory tract viruses) or that early ART can prevent OB. In our series from Harare, however, OB was not restricted to patients with low CD4 counts and did not appear to respond to ART once established. However, this was a cross-sectional study and little is known about the natural history of this condition.

Pronounced stunting and pubertal delay are also common. Catch-up growth and pubertal development are likely to be age-dependent, with less good outcomes reported when ART is started in older children and adolescents.22-23 Untreated HIV infection is characterised by pronounced chronic immune activation,24-26 and inflammatory conditions appear unusually common in older children, including seronegative arthritis, cerebral vasculitis and uveitis.7 These conditions result in severe disability and functional impairment.

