### 3.4.3 Clinical cohort study

The following outcomes will be determined for the clinical cohort:

- Mortality rate and cause of death
- Adherence rates
- Rate of failure of first-line ART
- Rates of incident opportunistic infections and tuberculosis
- Rates of hospital admission
- Rates of school attendance

In addition, the above outcomes and rate of lung function decline and rates of pubertal development and growth will be compared by ART status.

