## 7.5 Assessment of growth

All assessments of growth will be measured at baseline, before starting ART and at intervals specified in Table 7.1

Weight will be measured on every scheduled and unscheduled clinic visit using digital weight scales. Standing and sitting height (a measure of leg length)72 will be measured at every scheduled visit. Mid-upper arm circumference and head circumference will be measured six-monthly.

Puberty will be assessed annually using Tanner Staging.73 Tanner Staging will only be carried out in children who are ≥9 years. The following aspects of pubertal development will be recorded for males and females:

- Males- Testicular size (measured using a Prader orchidometer), Penile and pubic hair growth
- Females- Breast size and pubic hair growth; age of menarche

The Tanner pubertal stage recorded will be determined by breast development in females and testicular size in males

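### Section 9.1 defines wasting by weight-for-age, which measures underweight and mixes short stature with thinness, so some children can be misclassified in a population where stunting is common

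*Protocol*

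**What the plan says.** The definitions in Protocol section 9.1, under Outcome Evaluation, give stunting as "Height-for-age z-scores using WHO reference Standards" and, on the next line, wasting as "Weight-for-age z-scores using WHO reference Standards". Neither carries a cut-off. No BMI-for-age or weight-for-height index appears anywhere in the protocol.

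Growth enters the study through the third specific aim in section 1.2: "To assess the effect of ART on lung function and growth in HIV-infected children aged 6-15 years". Section 3.4.3 carries this into the cohort outcomes, where the "rate of lung function decline and rates of pubertal development and growth will be compared by ART status". On the population, section 2.2 states: "Pronounced stunting and pubertal delay are also common".

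On data collection, section 7.5 says of weight: "Weight will be measured on every scheduled and unscheduled clinic visit using digital weight scales". Standing and sitting height "will be measured at every scheduled visit". The same section adds: "Mid-upper arm circumference and head circumference will be measured six-monthly". Section 9.2.4 lists weight, height, both circumferences and pubertal stage among the recorded cohort variables.

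**The concern.** Wasting means low weight relative to height. Weight-for-age takes no account of height, so a short child of ordinary build has a low value. The index named in section 9.1 is a measure of underweight under another label, and it shares a component with the stunting definition beside it. No listed index isolates thinness.

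This matters more here than in a well-grown population, because the two indices diverge most in short children. If weight-for-age differs between children on and off ART, the difference may come from height, from body mass or from both. A result reported as wasting would invite the reader to take it as thinness alone.

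**Working it through.** The protocol attaches no figure to this definition, so there is nothing of its own to reproduce. The check asks how far weight-for-age can depart from thinness.

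**Inputs from the protocol:** wasting is weight-for-age z and stunting is height-for-age z, both without a cut-off (section 9.1).

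**Assumptions, none of them in the protocol:** a cut-off of -2; coefficients of variation around the age mean (used as log-scale standard deviations) of 4-5% for height and 11-13% for BMI; height and BMI independent in the reference population.

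**Formula.** Weight = BMI x height², so ln(weight) = ln(BMI) + 2 ln(height). With s_h and s_b the log-scale standard deviations of height and BMI:

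- SD of ln(weight) = √(s_b² + (2 s_h)²)
- weight-for-age z = (s_b x BMI z + 2 s_h x height z) / SD

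At the central values: SD = √(0.12² + 0.09²) = √0.0225 = 0.15. The weights are 0.12/0.15 = 0.80 on BMI z and 0.09/0.15 = 0.60 on height z.

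| Height CV | BMI CV | SD | Weight on BMI z | Weight on height z | A: height z -2.5, BMI z -1.0 | B: height z -2.5, BMI z 0 | C: height z 0, BMI z -2.3 |
|---|---|---|---|---|---|---|---|
| 4% | 13% | 0.153 | 0.85 | 0.52 | -2.16 | -1.31 | -1.96 |
| 4.5% | 12% | 0.150 | 0.80 | 0.60 | -2.30 | -1.50 | -1.84 |
| 5% | 11% | 0.149 | 0.74 | 0.67 | -2.42 | -1.68 | -1.70 |

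- Child A is stunted and not thin, yet falls below -2 in every row and would be classed as wasted.
- Child B is equally short and of average build, and stays above -2. On central values, an average-build child crosses only when height z is below -2/0.60 = -3.3 (range -3.0 to -3.8).
- Child C is of average height and thin by the same -2 cut-off on BMI z, yet stays above -2 on weight-for-age and would be missed.

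**Share of each component.** On central values BMI carries 0.80² = 0.64 of the reference variance of weight-for-age and height 0.60² = 0.36. Over the range, the height share runs from about 0.27 to 0.45.

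**Illustration in a simulated population.** This used a wider BMI range (log-scale SD 0.08-0.13), the same height range and cut-off, unit standard deviations for both z-scores, and mean height z and BMI z of either -1.0 and 0 or -1.5 and -0.5. Between 20% and 67% of stunted children who were not thin fell below -2 on weight-for-age, and between 8% and 37% of thin children did not. The width of these intervals shows how much the size depends on the assumptions.

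**The case against.** Several objections have force.

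- **Wasting is defined but not named as an outcome.** The cohort outcomes refer to rates of growth and pubertal development, and no section plans a proportion wasted. This stands. The definition nevertheless sits under Outcome Evaluation, so any wasting result would be expected to follow it.
- **No cut-off is given, so the protocol as written classifies no child.** This stands too. Cut-offs may be in the statistical analysis plan or the cohort SOPs, which are not shown, and their absence is not the point here. Because weight-for-age mixes height and thinness whatever threshold is applied, a cut-off elsewhere would not cure it.
- **A reader might infer that weight-for-age largely re-measures stunting, or that stunted children in general would be counted as wasted.** The arithmetic does not support either. BMI is the larger component on central values, and child B does not cross -2.
- **A reader might infer that an ART effect on thinness could no longer be separated from one on height.** The protocol does not support that. Height-for-age is defined separately, weight and height are recorded at every scheduled visit, and mid-upper arm circumference is measured six-monthly.
- **The example depends on independence.** If height and BMI correlated at +0.3 (an illustrative value), child A would score about -1.92 to -2.13, so at one end the child would no longer cross.
- **BMI-for-age is not a perfect substitute.** Section 2.2 also reports pubertal delay as common, and late maturation can lower BMI relative to age peers. This is a fair limit on the remedy, but BMI-for-age still removes the direct dependence on height.

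**Conclusion.** The definition does not match its label. Weight-for-age measures underweight and overlaps in part with the height-for-age definition of stunting. Where stunting is common, some stunted children who are not thin can be classed as wasted and some thin children who are not short can be missed. Under the stated assumptions the first error arises for a child with height z -2.5 and BMI z -1.0 (score -2.2 to -2.4), but not for one of the same height with BMI z 0 (about -1.3 to -1.7). The number affected cannot be derived from the protocol.

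The consequence is limited to how a wasting result would be read within the cohort growth comparison by ART status. A reader might extend it to the trial's conclusions, but the main outcomes in section 3.4.2 and the sample sizes in section 11.2 do not use this definition. It is a minor correction to a stated rule.

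**What to change.** In section 9.1, define wasting by a height-adjusted index: BMI-for-age z-score, computed from weight and standing height at the same scheduled visit, with its cut-off stated. If weight-for-age is kept as a further growth measure, label it underweight. Because pubertal delay is common here, read BMI-for-age alongside the pubertal stage already recorded; mid-upper arm circumference can serve as a supporting measure.

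The cost is a change of wording and one derived variable. It needs no new measurement, visit or participant, and leaves the sample size and the trial outcomes unchanged.

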## 9.2 Capture of Study Endpoints

### 9.2.1 PITC

The following data on all children who attend the PHC aged between 6-16 years will be collected on a study form by the research assistant:

- Age and sex of child
- Age, sex of accompanying person
- PITC offered or not
- PITC accepted or refused and reason for refusal (i.e., either know status already or refusal of parental consent or inappropriate guardian)
- HIV-test result of child
- HIV test result of guardian

The data collection process will thus ensure that children eligible for PITC are not missed.

The following will be determined among children aged 6-15 years:

- number who attend the PHC
- number who attend without a guardian
- number who assent but guardians do not consent
- number who assent to testing with guardian consent
- number who test HIV-positive

### 9.2.2 Trial

The cumulative total number of children aged 6-15 years offered PITC who test HIV-positive and are recruited into the study under the trial arms will be determined.

The following data on the children who test HIV positive through PITC will be collected on study forms:

- Recruited or not recruited into the study
- Study arm recruited
- Routine clinic appointment dates on the clinic card and the actual visit date
- Any additional study visits
- On ART or not started
- Date started on ART
- CD4 count
- Viral Load post 12months ART
- On first vs second-line ART
- Pill count
- Adherence assessment result

Further, HIV-positive participants in each arm started on ART and date started will be used to determine if the participant has been on ART for a period of one year or more. The cumulative total number of participants who have been on ART for a period of ≥1 year will be determined.

A field will be generated which calculates the number of days between the routine appointment date and the actual routine visit date. If the difference is more than 7 days, an appointment will be classified as missed. The cumulative number of missed appointments for each participant will be calculated; the proportion of participants with more than two missed appointments will then be calculated for each arm.

Another ART outcome field will be generated which determines if the viral load is >400 copies/ml or if the participant has died within a period of one year on ART. If this is true, the ART outcome will be classified failure otherwise it will classified as success or unknown if the participant is lost to follow-up.

If the patient has not attended for an appointment for a period of >6 months, they will be followed up to ascertain the cause of this (death/move out of area/default /other). If alive and still in the area, cause of default will be determined as well as relevant clinical information. If agreeable the current viral load will be determined and the participant encouraged to re-attend for HIV care.

If the participant has died and the family is still in the area, the date of death will be recorded and a brief verbal autopsy conducted to ascertain the cause of death.

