**ZENITH OUTCOMES**

1. **Impact of PITC (prevalence survey)**

- Proportion of HIV-infected children who are still undiagnosed
- Overall HIV prevalence

1. **Impact of VLW intervention**

- Retention into care: proportion of children with ≥2 missed routine clinic visits
- Failure to suppress viral load on ART
- Morbidity and mortality

1. **Pre-ART care cohort**

- New onset and worsening lung function test abnormalities
- Pubertal development and growth
- HIV-associated infections and mortality

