### 3.4.2 Individual-randomised trial of household support

The unit of randomization will be an individual attending each clinic, and not households, however, the trial outcomes will be evaluated at the level of the clinic to cater for any clustering at clinic (suburb) level. The main differences between the two arms will be:

- Proportion on ART with treatment failure defined as an HIV-1 viral load >400copies/ml at 12 months after starting ART or death in the first year of ART
- Proportion who miss two or more *routine* appointments by the end of two years of follow-up

Other comparisons between arms will include:

1. all-cause mortality
2. numbers of and time to first hospital admission (defined as stay in hospital for ≥24 hours)
3. numbers of additional attendances (over and above routine follow-up) to PHC
4. proportion of children who have an average adherence rate <80% 12 months after starting ART
5. proportion of children who change to 2nd line ART as defined by National Guidelines (due to reasons not related to toxicity, side-effects or starting TB treatment)

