## 11.2 Sample size estimates

### 11.2.1 Individual-randomised trial

A sample of 175 children with newly diagnosed HIV per arm provides 80% power to detect a 45% reduction in proportion of children who miss ≥2 routine appointments in the follow up period in the intervention arm relative to the standard of care arm, given the most likely scenario of 30% missing in the control arm 4, 86, and allow 10% loss to follow-up, assuming a baseline HIV prevalence of 1.8%. The study also has 83% power to detect a 40% difference in proportions who miss ≥2 appointments, assuming that rates in the unexposed arm is 40%.

Studies have shown virological failure rates of 30-70% in older children. 1, 87-88 Assuming that at least 70% of the 175 children per arm with newly diagnosed HIV start ART, we expect 123 children per arm to be on ART. If the treatment failure/death rate among controls is 50%, the study will have 87% power to detect a 40% reduction in this rate. Given that our retention rate into the trial is better than expected, 350 participants will therefore provide adequate power to detect the difference in retention in care between the trial arms, even with the lower sample size.

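### Section 9.2.2 derives the retention outcome as three or more missed appointments, although it is defined and powered as two or more, and its date-gap field gives no value for a visit never made

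*Protocol*

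**What the plan says.** The threshold appears in five places, and four agree:

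- Section 1.4 lists the outcome with a threshold of two or more.
- Section 3.4.2 has it as "Proportion who miss two or more" routine appointments.
- Figure 1.1 has "proportion of children with ≥2 missed routine clinic visits".
- Section 11.2.1 bases the sample size on the "proportion of children who miss ≥2 routine appointments in the follow up period".
- Section 9.2.2, on endpoint capture, differs: "the proportion of participants with more than two missed appointments will then be calculated for each arm".

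A single miss is described twice. Section 9.1 defines it by non-attendance: "Participant fails to attend a routine appointment within 7 days of a scheduled appointment" (with a parallel clause for ART refill visits). Section 9.2.2 builds a field that "calculates the number of days between the routine appointment date and the actual routine visit date" and then applies a cut-off: "If the difference is more than 7 days, an appointment will be classified as missed". It does not say what the field holds when there is no actual visit.

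**The concern.** A child with exactly two missed appointments has the event under sections 1.4, 3.4.2 and 11.2.1 and Figure 1.1, but not under the derivation in 9.2.2. The two rules cannot both be followed. Two analysts, one working from 3.4.2 and the other from 9.2.2, would report different retention results from the same data. If the choice were made after the data were seen, it would invite a charge of selective definition. The sample size also rests on this outcome, so applying the stricter threshold lowers the event rate in both arms and costs power.

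The second issue is narrower. A date difference needs two dates. For an appointment that is never attended there is only one, so the difference cannot exceed 7 days and the literal rule does not flag a miss. The definition in 9.1 needs no later visit and would count it. The children affected are those who stop coming, and retaining them is what the intervention is for.

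**Working it through.** **1. Reproduce the stated power (outcome of two or more misses).**

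Inputs from 11.2.1: 175 per arm, control proportion 30%, 45% relative reduction, 10% loss to follow-up. Allocation is 1:1 (3.3). No significance level is stated there, so two-sided 5% is assumed.

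- Intervention proportion: 0.30 × (1 − 0.45) = 0.165.
- Evaluable per arm: n = 175 × 0.90 = 157.5.
- Power = Φ{[p₁ − p₂ − 1.96·√(2p̄(1−p̄)/n)] / √[(p₁(1−p₁) + p₂(1−p₂))/n]}, with p̄ = (0.30 + 0.165)/2 = 0.2325.
- Standard errors: 0.0476 (pooled) and 0.0470 (unpooled).
- (0.135 − 1.96 × 0.0476)/0.0470 = 0.887, and Φ(0.887) = 0.813.

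This gives 81.3% against a stated 80%, so the stated figure reproduces. In the other direction, the same formula at 80% power needs 153 per arm, and 153/0.90 = 170, close to 175.

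**2. Apply the threshold written in 9.2.2 (three or more misses).**

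The protocol does not give the distribution of the number of misses per child, so a model has to be assumed. Misses are taken as binomial (correlation 0) or beta-binomial (correlation above 0) over K routine visits. The mean miss probability in each arm is set so that P(≥2) equals 30% and 16.5%. P(≥3) is then read off and the power formula above applied with n = 157.5. K = 9 or 10 matches the column headings after week 0 in Tables 7.1 and 7.2; 7 and 8 are added for range.

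| K | Correlation | P(≥3) control | P(≥3) intervention | Power |
|---|---|---|---|---|
| 7 | 0 | 8.1% | 3.0% | 51% |
| 7 | 0.2 | 16.5% | 8.1% | 62% |
| 7 | 0.4 | 21.0% | 10.9% | 69% |
| 9 | 0 | 8.6% | 3.2% | 53% |
| 9 | 0.2 | 18.0% | 9.0% | 65% |
| 9 | 0.4 | 22.1% | 11.6% | 71% |
| 10 | 0 | 8.7% | 3.2% | 53% |
| 10 | 0.2 | 18.5% | 9.3% | 65% |
| 10 | 0.4 | 22.5% | 11.9% | 71% |

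Values for K = 8 lie between those for 7 and 9. In the middle row (K = 9, correlation 0.2), 30.0 − 18.0 = 12.0 percentage points of control children and 16.5 − 9.0 = 7.5 points of intervention children have exactly two misses. These are the children the two rules classify differently.

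**3. The date-gap field against the 9.1 definition.**

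| Situation | Section 9.1 | Section 9.2.2, read literally |
|---|---|---|
| Attends within 7 days | Not missed | Gap ≤ 7: not missed |
| Attends more than 7 days late | Missed | Gap > 7: missed |
| Never attends that appointment | Missed | No gap exists: no rule |

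The two agree except in the last row. Elsewhere in 9.2.2 the ART outcome field has an explicit category for children lost to follow-up, but the missed-appointment field has none. Children absent for more than 6 months are traced for the reason, but the protocol does not say how they enter this outcome or whether appointments continue to accrue for them. No default rate is given for either arm, so no figure can be derived.

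**The case against.** On the threshold, the best reply is that 9.2.2 contains a slip of wording and that four other places show what was meant. That is probably so. But 9.2.2 is where the derivation is spelled out, and the slip changes who has the event, so it still has to be corrected.

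On the power figures, it is fair to say that they rest on assumed visit counts and correlations. The lowest values need misses to be independent within a child, which is hard to believe for attendance behaviour. Stronger correlation narrows the loss: at 9 visits and correlation 0.6, power is about 75%. The direction is the same in every case examined, but no single value should be taken as the trial's power.

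A reader might go further and infer that permanent defaulters will be scored as retained. The documents do not support that. Section 9.1 counts a failure to attend as a miss without needing a later visit, 7.2 offers alternative appointments after a missed one, and 9.2.2 has long absentees traced. How a blank visit date is coded could also reasonably be left to an analysis plan or database specification. What stands is that the field as described does not cover the case that 9.1 covers, and that nothing fixes how appointments accrue after a child stops coming. Any power figure for this effect would need invented default rates, and would have to avoid double-counting the 10% loss already removed from the sample.

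A reader might also infer that the sample size is wrong. It is not: it reproduces for the outcome it names.

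**Conclusion.** The threshold in 9.2.2 is wrong as written. It contradicts the outcome definition in sections 1.4 and 3.4.2, Figure 1.1 and the sample size in 11.2.1. If followed, power for the planned effect falls from about 81% to roughly 51–71%, assuming two-sided 5%, 157.5 evaluable children per arm, 7 to 10 routine visits and within-child correlation of 0 to 0.4.

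The missing rule for unattended visits is a smaller, real inconsistency with 9.1. Taken literally it could under-count misses in children who stop attending, by an amount the protocol does not allow one to estimate. Because the outcome is one of the two main comparisons and carries the sample size, the wording should be corrected before the outcome is derived.

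**What to change.** In section 9.2.2:

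1. Change the threshold from more than two to two or more missed appointments, matching 3.4.2 and 11.2.1.
2. State that a scheduled routine appointment with no attendance within 7 days counts as missed, as in 9.1, even when there is no later visit date.
3. Fix in advance how scheduled appointments are handled after default, death or moving away, with the same rule in both arms.

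Attendance can still be measured against the appointments on the clinic card. Replacing these with fixed calendar dates is not needed to repair the inconsistency. If later visits are booked from an earlier late one, it could mark a child who then kept every booked appointment as repeatedly missing.

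The cost is protocol wording and derivation code. No new data and no change in sample size are required.

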## 4.5 Participant selection, inclusion and exclusion criteria

The inclusion criteria for participation in the trial will be:

- age between 6 years (day of their 6th birthday and older) and 15 years (a day before their 16th birthday)
- test HIV-positive following PITC in the PHC
- willing to have their HIV care at the PHC
- usual residence in the study suburb where the PHC is located
- informed consent by parent and assent from child to participate

The exclusion criteria for participation in the trial will be:

- age <6 years or ≥16 years
- usual residence outside the study suburb where the PHC is located
- previously tested HIV+ positive and receiving care (clinical or psychosocial)
- not planning to access HIV care at the PHC

All participants enrolled into the trial will automatically be offered enrolment into the cohort study. Additionally, any children aged 6-15 years who test HIV-positive following PITC after enrolment for the trial is completed, will also be approached for recruitment into the clinical cohort study.

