## 7.3 PHC Patients not enrolled in cohort study

Patients who register for HIV care at the PHC, but decline consent to participation into the cohort study will be receive the same level of care as participants enrolled into the clinical cohort. However, the following will not be carried out:

- Assessment of lung function
- Detailed growth and pubertal staging
- Viral load testing one year after starting ART
- Blood sampling for immunogenetic studies
- Detailed psychosocial and adherence assessment

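### The ART outcome field in section 9.2.2 codes a child in care with no viral load as a success, and sections 7.3 and 9.2.2 conflict on whether every trial child on ART is to be tested

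*Protocol*

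**What the plan says.** The outcome is defined in section 3.4.2 (and in 1.4) as "Proportion on ART with treatment failure defined as an HIV-1 viral load >400copies/ml at 12 months after starting ART". A child who dies within that first treatment year also counts as a failure.

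Section 9.2.2 turns this into a derived field, which "determines if the viral load is >400 copies/ml or if the participant has died within a period of one year on ART". If so, "the ART outcome will be classified failure otherwise it will classified as success or unknown if the participant is lost to follow-up". The field has three values. None is reserved for a child who is in care but has no result.

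Three places bear on who gets the test:

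- Section 7.3 concerns "Patients who register for HIV care at the PHC, but decline consent to participation into the cohort study". Its list of procedures not carried out for them includes "Viral load testing one year after starting ART" and the detailed adherence assessment.
- Section 4.5 says "All participants enrolled into the trial will automatically be offered enrolment into the cohort study". Enrolment is offered rather than required, and section 14.2 lists consent for the trial and for the cohort assessments as separate items.
- Section 9.2.2, under the trial heading, lists "Viral Load post 12months ART" and the adherence assessment result among the data collected on children who test positive.

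Section 11.2.1 gives 87% power to detect a 40% reduction from a 50% failure rate, on the basis that "we expect 123 children per arm to be on ART".

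**The concern.** Success on this outcome should mean a viral load that was measured and was not above the threshold. As written, success is the default for anyone not shown to have failed and not lost. An attending child whose sample was never taken, was spoiled or was not reported is counted as suppressed. The definition in section 3.4.2 rests on a 12-month measurement or a death, and the derived field departs from it.

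The protocol also leaves open a route by which a randomised child on ART has no planned test: consent to the trial, decline the cohort, and fall under the section 7.3 list. The same list removes the detailed adherence assessment, which bears on the comparison of adherence below 80% at 12 months.

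At stake are the failure proportions in both arms, the absolute difference between them and the power to detect it. The risk ratio is also at stake if the share without a result differs by arm, which is plausible because the intervention aims to change attendance.

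**Working it through.** **Inputs from the protocol.** 175 children per arm, 70% starting ART, so 0.70 × 175 = 122.5, taken as 123. Control failure/death 50%. A 40% relative reduction gives 0.50 × 0.60 = 30%. Stated power 87% (all section 11.2.1). Allocation 1:1 (section 5.3).

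**Assumptions.** Two-sided 5% test, since the protocol states neither alpha nor sidedness. The share of failing children with no result, *m*, is an assumed range, since the protocol gives no missing rate. All failure is treated as virological. Deaths are captured without a viral load, so to the extent that failures are deaths, the shrinkage below is a little overstated.

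**Power formula.** Normal approximation with continuity correction, p̄ = (p₁ + p₂)/2:

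power = Φ{ [ |p₁ − p₂| − 1/n − 1.96 √(2p̄(1 − p̄)/n) ] / √[(p₁(1 − p₁) + p₂(1 − p₂))/n] }

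**Reproducing the stated figure.** With n = 123, p₁ = 0.50 and p₂ = 0.30, the numerator is 0.200 − 0.0081 − 0.1224 = 0.0694 and the denominator is √(0.46/123) = 0.0612. The ratio is 1.135 and power is 87.2%, which matches the stated 87%. Without the correction it is 89.8%. All power figures below use the corrected scale.

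**Effect of coding no result as success.** Observed failure = true failure × (1 − *m*). With the same *m* in both arms:

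| *m* | Control | Intervention | Difference (points) | Risk ratio | Power, coded success | Power, left out as missing |
|---|---|---|---|---|---|---|
| 0% | 50% | 30% | 20 | 0.60 | 87% | 87% |
| 5% | 47.5% | 28.5% | 19 | 0.60 | 84% | 85% |
| 10% | 45% | 27% | 18 | 0.60 | 81% | 83% |
| 20% | 40% | 24% | 16 | 0.60 | 73% | 78% |
| 30% | 35% | 21% | 14 | 0.60 | 64% | 72% |

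The last column uses n = 123 × (1 − *m*) at 50% v 30%. Default-to-success costs more power than treating the same children as missing.

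**Unequal missingness, no true effect (50% in both arms).** With 5% missing in control and 15% in intervention, observed failure is 0.50 × 0.95 = 47.5% v 0.50 × 0.85 = 42.5%, a spurious risk ratio of 0.85/0.95 = 0.89. Reversed, it is 0.95/0.85 = 1.12. The chance of a significant result in the distorted direction is about 10%, against a nominal 2.5%.

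**Unequal missingness, true 50% v 30%.** The same two patterns give 0.255/0.475 = 0.54 and 0.285/0.425 = 0.67 in place of 0.60.

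**Loss in the power statement.** The 10% loss in section 11.2.1 is attached to the missed-appointment calculation only. Applied here, 0.90 × 123 = 110.7, taken as 111 per arm. The ratio becomes 0.0621/0.0644 = 0.965 and power is about 83%.

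**The case against.** The best case for the plan has four parts.

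**The test is listed as trial data.** A reader of section 7.3 alone might infer that the viral load is withheld from trial children by design. The protocol does not settle that. Section 9.2.2 lists both the viral load and the adherence result under the trial. Sections 1.3 and 3.3 expect trial children to be recruited into the cohort. Section 7.3 sits in the cohort chapter and does not mention trial participants. What stands is a conflict for a randomised child who declines the cohort. How many would decline is not stated, and it may be few.

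**Unknown is a fair label for a lost child.** A reader might infer that children coded unknown are dropped from the analysis, to the detriment of an arm comparison that turns on retention. The protocol assigns the label and does not say they are excluded. Their handling may sit in a statistical analysis plan that is not available here. Section 9.2.2 also provides for tracing after more than six months without attendance, with deaths ascertained and a current viral load taken if the family agrees. That reduces the unknown group, although the section does not say how a traced value enters the outcome field.

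**Bias is conditional.** If missingness is equal between arms and unrelated to failure, the risk ratio stays at 0.60. It would be too strong to say that the comparison is biased. The failure proportions, the risk difference and power still suffer.

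**Power remains acceptable with ordinary loss.** At 83% it is above the 80% used for the other main outcome. This is correct, so the power figure is a matter of restatement and not a shortfall.

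None of this answers the central point: the written rule records an unmeasured child in care as a success.

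**Conclusion.** The point holds in a limited form and should be fixed. Section 9.2.2 fixes a derivation in which success needs no measurement, and sections 7.3 and 9.2.2 disagree on whether every randomised child on ART has the test that the outcome needs. Failure is understated in an arm whenever a truly failing child in care has no result. Under assumed missingness of 10% to 20%, equal in both arms, the risk difference falls from 20 points to 18 and 16, and power from 87% to about 81% and 73%. A 10-point gap in missingness between arms would move a true risk ratio of 1.00 to 0.89 or 1.12. These sizes rest on the protocol's planning rates, a two-sided 5% test and assumed missing rates. The actual size cannot be found from the document. The stated 87% is arithmetically right but presumes a classifiable outcome for all 123 children per arm.

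**What to change.** 1. In section 9.2.2, code success only on a measured viral load of 400 copies/ml or less. Code a child in care without a result as missing. Keep unknown for children lost to follow-up, and say how a viral load obtained by tracing enters the field.
2. Reconcile section 7.3 with section 9.2.2, and adjust the consent wording, so that the 12-month viral load and the adherence assessment are trial procedures for every randomised child on ART, whether or not the family joins the cohort.
3. Leave the primary outcome definition as it stands. Report sensitivity analyses for missing and unknown outcomes, for example multiple imputation and missing counted as failure. Counting children out of care as failures in the primary analysis would change the defined outcome and make it overlap with the missed-appointment outcome.
4. Restate power in section 11.2.1 with the 10% loss used for the other main outcome: 111 per arm, about 83%.

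The cost is a wording change to the protocol and consent forms, viral loads and adherence assessments for the trial children who decline the cohort, and a slightly lower stated power.
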